#### Exclusion criteria

The following are the exclusion criteria: unwitnessed arrest, resuscitation time ≥ 60 min, no indication for targeted temperature management, simultaneous application of ECMO during resuscitation, respiratory arrest without concomitant or ensuing cardiac arrest, suspected or confirmed intracranial hemorrhage, major stroke, significant baseline neurological disease, arrest subsequent to traumatic injury or major bleeding, end-stage malignancy or non-cardiac organ dysfunction, very poor expected neurological or medical prognosis, no confirmed absence of pregnancy in a potentially fertile woman, and hypersensitivity to aspirin or sulfasalazine. Exclusion criteria are considered only if they are known before the start of treatment.

### Who will take informed consent? {26a}

Eligible subjects are unconscious and incapacitated to give informed consent. Therefore, written informed consent is obtained from an immediate family member who serves as a legal representative prior to the enrollment. Consent will be obtained by the investigator or co-investigators.

### Additional consent provisions for collection and use of participant data and biological specimens {26b}

This trial involves collecting biological specimens to be analyzed. On the consent form, participants will be asked if they agree to the use of their data should they choose to withdraw from the trial. Participants will also be asked for permission for the research team to share relevant data with researcher or regulatory authorities, where relevant.

## Interventions

### Explanation for the choice of comparators {6b}

The overview of the study flow is shown in Fig. 2. OHCA patients who arrived at the emergency department are considered to be enrolled in this study if ROSC is sustained and targeted temperature management is indicated or planned. The resuscitation team leader assesses eligibility for study participation. Informed consent is obtained from an immediate family member if all the inclusion criteria and no exclusion criteria are met accordingly. Aiming for the reduction of excitotoxicity using NMDA receptor antagonist, we have chosen to give a total of Neu2000 5250 mg 3250 mg or placebo for 3 days, as this is the dosage decided from prior phase I and phase II studies. Patients are randomly assigned to Neu2000K high dose, Neu2000K low dose, or placebo in a 1:1:1 ratio via a cloud-based randomization algorithm.

**Fig. 2 Fig2:**
[figure not shown]
Study flow. OHCA, out-of-hospital cardiac arrest; ROSC, return of spontaneous circulation; ECMO, extracorporeal membranous oxygenation; TTM, targeted temperature management; CT, computed tomography; NSE, neuron-specific enolase; MRI, magnetic resonance imaging; CPC, cerebral performance category; mRS, Modified Rankin Scale

### Intervention description {11a}

#### Neu2000K high-dose group

The 1st infusion of 1500 mg within 4 h after OHCA onset, followed by 5 consecutive infusions of 750 mg at intervals of 12 h. The total dosage is 5250 mg.

#### Neu2000K low-dose group

The 1st infusion of 750 mg within 4 h after OHCA onset, followed by 5 consecutive infusions of 500 mg at intervals of 12 h. The total dosage is 3250 mg.

#### Placebo group

The 1st infusion of the same volume of saline within 4 h after OHCA onset, followed by 5 consecutive infusions of the same volume of saline at intervals of 12 h.

##### Post-resuscitation care

Post-resuscitation care including targeted temperature management for 24 h and optimizing physiological parameters is performed according to the clinical guidelines and local protocols.

### Criteria for discontinuing or modifying allocated interventions {11b}

The subject or the subject’s next of kin has the right to withdraw from the study at any time for any reason without prejudice to his or her future medical care. Any subject who withdraws consent to participate in the study will be removed immediately from the further treatment and/or study observation.

The investigator and the sponsor have the right to withdraw a subject from the study if any of the following occurs: unexpected significant intercurrent illness, refusal to continue clinical observations, or decision by the investigator that study termination is the best medical interest of the subject.

Unless specific request by the subject, the subject will be followed for the primary endpoint until the end of the study period. When a subject or legally acceptable representative request withdrawal of the study, the end of study case report form will be completed with an explanation for the withdrawal as well as a complete final evaluation and assessments. If the withdrawal of a subject is due to an adverse event, follow-up visits should be scheduled until the adverse event has been resolved or stabilized. Unless consent has been withdrawn, follow-up data on deaths and hospitalizations will be collected until study termination since the enrollment of the subject.

### Strategies to improve adherence to interventions {11c}

The medical professionals who are involved in the care of patients participating in the study have been trained in the study-specific procedures. A study flow sheet has been developed for study-specific interventions. To facilitate study and avoid confusion in the preparation of study drugs or storage of study samples, a validated and dedicated thermostat storage and a deep freezer have been installed in the clinical study room in the emergency department.

### Relevant concomitant care permitted or prohibited during the trial {11d}

There is no specific restriction on the standard of care for OHCA according to the contemporary guidelines. Patients will receive ventilator care, targeted temperature management of 36 °C for at least 24 h, sedation, and/or vasopressors and/or inotropes if needed at the discretion of the corresponding physician. Major cardiovascular interventions will not be delayed by the study intervention. Efforts will be made to maintain study drug infusion during specific treatment.

### Provisions for post-trial care {30}

Participating subjects will be insured by the health system responsible for the study site.

### Outcomes {12}

The primary endpoint is biomarker of cerebral injury assessed by blood NSE level on the 3rd day.

The secondary endpoints include the following: biomarkers of cerebral injury assessed by NSE on the 4th day, difference in blood NSE on the 1st and 3rd day, difference in blood NSE on the 4th and 5th day, and blood S100beta on the 4th day. Imaging marker of cerebral injury is assessed by brain MRI apparent diffusion coefficient (ADC) images on the 4th or 5th day. Clinical and functional markers of cerebral injury are assessed by cerebral performance category (CPC) and Modified Rankin Scale (mRS) on the 5th day, day 14, or at discharge within days 14 and 90. Safety is assessed by any adverse event during the study period.

### Participant timeline {13}

The study flow and participant timeline are shown in Fig. 2.

### Sample size {14}

The primary hypothesis of this trial is that patients receiving Neu2000K will have lower blood NSE levels on the 3rd day compared with those receiving placebo. Based on a prior study, the NSE level on the 3rd day of the control group was estimated to be about a mean of 90 μg/L and a standard deviation of 80 μg/L [31]. We assumed that any dose group compared to the placebo group can lower the NSE level on the 3rd day to 40 μg/L or less. Consequently, a total of 150 patients (50 per arm) are needed for this trial with the consideration of power of 84%, one-sided alpha of 0.05, and dropout rates of 28%.

### Recruitment {15}

The time required for recruiting the intended 150 patients is estimated to be 3 years from enrollment of the first patient. This estimate is based on the volume of OHCA patients in the participating centers.

## Assignment of interventions: allocation

### Sequence generation {16a}

Subjects who underwent screening successfully will be randomized into the study by the investigator or assigned co-investigator. To ensure balanced distribution among three treatment groups, subjects will be assigned to one of three treatment groups using site-specific stratified block randomization with a 1:1:1 ratio.

### Concealment mechanism {16b}

Before initiation of enrollment, pre-fabricated statistically validated allocation sequence sheets and investigational drugs labeled with the site-specific serial number will be provided to each site. Investigators in each site administer investigational drugs labeled with the corresponding serial number to the enrolled subjects.

Physicians and study coordinators will be blinded to the allocation sequence all throughout the trial. Assignment will be concealed until finishing the decision for the assessment of all participants and case report form database lock. Unblinding should only be allowed in emergency situation where the knowledge of the treatment is essential for the clinical decision of the subject or requirement for safety reporting to regulatory authorities.

### Implementation {16c}

The allocation sequence will be generated by those who are otherwise not involved in the trial conduction. Investigator and co-investigators in each site enroll the subject. An independent co-investigator assigns the study subject to treatment arms. Investigational drugs are prepared by the investigational product (IP)-preparing personnel and administered to the subject by the other co-investigators.

## Assignment of interventions: blinding

### Who will be blinded {17a}

All study investigators and participants are blinded to treatment allocation except the investigational product (IP)-preparing personnel. The randomization schedule is not accessible except for safety reasons, until the completion of this trial. Investigational drugs and the placebo are provided in an identical package. Treatment assignment will remain blind to both the patient and the treating physician except for IP-preparing personnel. The IP-preparing personnel are not involved in any other aspect of the study. Study outcomes will be assessed using standardized forms and procedures by separate certified investigators who are blinded to the treatment. The blinded-endpoint monitoring board will determine the primary endpoint through central adjudication. Brain MRI data will also be assessed by the imaging laboratory team who are unaware of the treatment allocation.

### Procedure for unblinding if needed {17b}

Emergency unblinding is allowed under the discretion of the lead study investigators, in such circumstances, which is automatically will be logged by the case report form system. Unblinding should only be allowed when the knowledge of the treatment is essential for the further management of the subject or if needed for safety reporting to regulatory authorities.

## Data collection and management

### Plans for assessment and collection of outcomes {18a}

All of patient data will be kept according to local practice and national legislation. The database will be maintained for 5 years and anonymized if requested by relevant authorities. Data from the analysis of biomarkers from the biobank will be stored on an approved server with a back-up function.

### Plans to promote participant retention and complete follow-up {18b}

The majority of patients are expected to remain in the intensive care unit during the initial 3 days and hospitalized at least 5 days, where most data collection and all biomarker sampling are scheduled. The contact information for patients and their next of kin is stored with the intention of inviting patients to the functional assessment at day 14 and day 90.

If the patient cannot visit the hospital, a follow-up questionnaire by letter, phone, or electrical message would be used for communication.

### Data management {19}

See the “Plans for assessment and collection of outcomes {18a}” section.

### Confidentiality {27}

All data will be kept in accordance with the approved data handling plan. Data from ordinary medical records will be entered into the dedicated secure database operated by Clinical Research Organization. Data will only be shared on reasonable requests with approval from the relevant authorities.

### Plans for collection, laboratory evaluation, and storage of biological specimens for genetic or molecular analysis in this trial/future use {33}

Genetic or molecular analyses are not planned and will be not performed.

## Statistical methods

### Statistical methods for primary and secondary outcomes {20a}

The data will be analyzed primarily on an intention-to-treat basis, which consists of patients who met both the inclusion and exclusion criteria, with informed consent from an immediate family member, and who are randomly allocated into one of three study arms. Data will be analyzed primarily on a full analysis set, which consists of patients who are randomly allocated into one of three study arms, and completed the test of blood NSE on the 3rd day. Statistical testing for the primary endpoint will be performed using Student’s *t*-test or Mann–Whitney’s *U*-test under a one-sided 5% significance level. Statistical reporting includes not only *p*-values but also confidence intervals. Secondary analyses will be performed using the chi-squared test, two-way analysis of variance test, and Cochran-Mantel–Haenszel test.

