### Trial design {8}

The Antioxidant and NMDA receptor blocker Weans Anoxic brain damage of KorEa OHCA patients (AWAKE) trial is a sponsor-initiated, randomized, placebo-controlled, double-blinded, prospective, intention-to-treat, three-armed, safety and efficacy clinical phase II trial.

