### Methods in analysis to handle protocol non-adherence and any statistical methods to handle missing data {20c}

Due to the extremely high early mortality of OHCA, the per-protocol analysis will consist of patients who received more than 80% of the planned study drug administration (5 or 6 infusions of the study drug or placebo). Any alternative method for missing values will not be used.

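### The primary NSE test uses only patients alive and sampled on day 3, about 108 of 150 on the plan's own figures, so it is not the intention-to-treat comparison that the protocol names

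*Protocol article*

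**What the plan says.** The Protocol article, Trial design {8}, describes a "randomized, placebo-controlled, double-blinded, prospective, intention-to-treat, three-armed, safety and efficacy clinical phase II trial".

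Statistical methods {20a} then names a primary analysis set twice, in consecutive sentences:
- "The data will be analyzed primarily on an intention-to-treat basis, which consists of patients who met both the inclusion and exclusion criteria", with family consent and random allocation as the further conditions;
- a full analysis set, also called primary, of "patients who are randomly allocated into one of three study arms, and completed the test of blood NSE on the 3rd day".

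Outcomes {12} states: "The primary endpoint is biomarker of cerebral injury assessed by blood NSE level on the 3rd day". It makes no provision for a patient who dies before that sample.

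The section on non-adherence and missing data {20c} says "Any alternative method for missing values will not be used". The same section explains its per-protocol rule with the words "Due to the extremely high early mortality of OHCA".

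Sample size {14} allows for 28% dropout. The Abstract calls the same 28% withdrawal before the endpoint.

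**The concern.** Two different sets cannot both be primary. The second is defined by something that happens after randomisation, namely having a day-3 blood sample. Because no missing-value method is allowed, the conflict has only one practical outcome. A patient without a day-3 NSE adds nothing to the test under either label.

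In this population the missing patients are unlikely to be a random subset. Early death and high NSE can both reflect severe brain injury. If a dose changes the chance of dying before day 3, the patients left in each arm are no longer comparable. A dose that adds early deaths among the worst injured would lower the mean NSE of those who remain and could look neuroprotective. A dose that keeps such patients alive would raise it and could look ineffective. Readers would take the result as protected by randomisation because the protocol calls it intention-to-treat.

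**Working it through.** **1. The plan's own figure.** Inputs from Sample size {14}: control mean 90 μg/L, treated mean 40, SD 80, one-sided alpha 0.05, power 84%, dropout 28%.

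- Evaluable per arm: n = 2 × (1.645 + 0.994)² × (80/50)² = 35.7, so 36.
- Inflated for loss: 36 / 0.72 = 50 per arm, and 3 × 50 = 150.

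The stated 150 is reproduced. The design therefore already counts on 3 × 36 = 108 patients in the NSE test.

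**2. Patients left out.** 0.28 × 150 = 42 in total, or 14 per arm.

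**3. Does the intention-to-treat label change this?** No. A patient in the intention-to-treat set without a day-3 value has no NSE to analyse, and {20c} allows nothing in its place. Both sets give the same test on the same patients.

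**4. What the loss consists of.** The documents give no split by cause. Two statements bear on it. Section {20c} acknowledges very high early mortality, although in the sentence about the per-protocol set. The section on retention {18b} expects most patients to be in intensive care for the first 3 days and in hospital for at least 5, which leaves limited room for ordinary loss to follow-up by day 3. Death is therefore a plausible main cause, but not a documented one.

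**5. Illustration of the bias.** These assumptions are not in the documents: day-3 NSE is log-normal with mean 90 and SD 80 (σ² = ln(1 + (80/90)²) = 0.582, μ = ln 90 − 0.582/2 = 4.209). All loss is death. Death before day 3 follows a probit model with latent correlation ρ to log NSE. There are 50 patients per arm, 28% loss on placebo, and no drug effect on NSE. The table shows how often the one-sided 5% test (t or Mann–Whitney, sampled patients only) favours the drug, by simulation with several thousand trials per scenario.

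| Loss on drug | ρ = 0 | ρ = 0.3 | ρ = 0.5–0.7 |
|---|---|---|---|
| 28% (equal) | about 5% | about 5% | about 5% |
| 38% | about 5% | 6–8% | 9–13% |
| 48% | about 5% | 8–10% | 13–25% |
| 18% | about 5% | about 3% | 1–3% |

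Bias needs both a difference in loss between arms and a link between loss and NSE. In the last row the drug prevents deaths, and at ρ = 0.5–0.7 the mean NSE of its sampled patients is about 5–6 μg/L higher than on placebo.

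**6. The worst-rank alternative.** Same model, Mann–Whitney test on all 50 versus 50 with early deaths ranked worst.
- No NSE effect, drug adds deaths: rejects in at most about 1.4% of trials.
- No NSE effect, drug prevents deaths (18% versus 28%): rejects in about 13–17% at ρ = 0.5–0.7, and a little over 20% at ρ = 0.
- Power at 90 to 40 with equal 28% loss and constant coefficient of variation: about 81–88%.
- Power at 90 to 60: about 37–46%, against 70–80% for the rank test in sampled patients.

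**The case against.** The strongest reply is that NSE among those sampled is a defensible endpoint for a phase II biomarker trial, and that deaths are visible elsewhere. Deaths are followed to study end unless consent is withdrawn {11b}. Death counts as a serious adverse event, with daily assessment for the first 5 days {22}. CPC and mRS are secondary endpoints. Sensitivity analyses are often left to the SAP, which is not shown. Much of this stands. It argues for labelling the set correctly and against forcing a new primary test. It does not remove the defect, because the article itself fixes the set, calls it primary beside a different one, and bars other handling of missing values. Those are stated rules and not details left open.

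A reader might infer more than the documents support, in four ways:
- **That the 28% is mostly death.** The Abstract says withdrawal, Sample size {14} says dropout, and neither gives causes. The exclusion of patients with very poor expected prognosis {10} also limits the inference.
- **That the result will be biased in a known direction.** With equal loss, or no link between loss and NSE, the test keeps its 5% level. The documents contain no mortality figure by arm.
- **That the intention-to-treat set drops randomised patients for ineligibility.** The wording permits that reading. But only subjects who pass screening are randomised {16a}, consent precedes enrolment {26a}, and exclusion criteria count only if known before treatment starts {10}. The sentence mostly describes who is randomised, and no material loss is shown.
- **That a worst-rank test must become primary.** It answers a different question, because it can reject when the drug only prevents deaths. It also loses much power at effects smaller than the planned one.

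**Conclusion.** The point holds in this form. The protocol names two primary sets, and its ban on missing-value methods reduces both to patients alive and sampled on day 3. On its own 28%, about 42 of 150 randomised patients fall outside the primary comparison, so the intention-to-treat label is not earned for that comparison. That much rests on the text and simple arithmetic.

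The size and direction of any bias are not known from the documents. The rejection rates in the table illustrate what could happen if loss differs between arms by 10 to 20 percentage points and is correlated with NSE. At weak correlation the distortion is small. At correlation 0.5–0.7 a nominal 5% test can reach roughly 9–25%. The sample size is not in question on the inputs of Sample size {14}.

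**What to change.** Before database lock:

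1. State one primary set and name it for what it is: randomised patients with a day-3 NSE. Stop describing the primary NSE comparison as intention-to-treat.
2. Delete the sentence in {20c} that rules out other missing-value methods.
3. Prespecify a sensitivity analysis in all randomised patients, stratified by site, in which death before the day-3 sample takes the worst rank. Give a separate rule, for example multiple imputation, for living patients who withdraw or miss the sample.
4. Report deaths and other losses to day 3 by arm beside the primary result. Make no claim of neuroprotection if the sensitivity analysis points the other way.

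The cost is wording and a little more analysis, with no new data. The worst-rank analysis has less power than the test in sampled patients and mixes mortality with NSE. It should therefore support the primary test and not replace it.

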**Methods:**

The aim of this study is to assess the feasibility and potential for reduction of ischemic brain injury in adult OHCA patients treated with high- or low-dose Neu2000K, a selective blocker of *N*-methyl-d-aspartate (NMDA) type 2B receptor and also a free radical scavenger, or given placebo. This study is a phase II, multicenter, randomized, double-blinded, prospective, intention-to-treat, placebo-controlled, three-armed, safety and efficacy clinical trial. This trial is a sponsor-initiated trial supported by GNT Pharma. Successfully resuscitated OHCA patients aged 19 to 80 years would be included. The primary outcome is blood neuron-specific enolase (NSE) level on the 3rd day. The secondary outcomes are safety, efficacy defined by study drug administration within 4 h in > 90% of participants, daily NSE up to 5th day, blood S100beta, brain MRI apparent diffusion coefficient imaging, cerebral performance category (CPC), and Modified Rankin Scale (mRS) at 5th, 14th, and 90th days. Assuming NSE of 42 ± 80 and 80 ± 80 μg/L in the treatment (high- and low-dose Neu2000K) and control arms with 80% power, a type 1 error rate of 5%, and a 28% of withdrawal prior to the endpoint, the required sample size is 150 patients.

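### The primary test is left as a raw-scale t-test or a Mann–Whitney test with no rule to choose, and omits the site strata; one fixed, site-adjusted analysis of log NSE would be better

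*Protocol article*

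**What the plan says.** All references are to the protocol article.

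- *Statistical methods for primary and secondary outcomes {20a}*: "Statistical testing for the primary endpoint will be performed using Student’s *t*-test or Mann–Whitney’s *U*-test under a one-sided 5% significance level". No transformation, covariate or stratum is named. Two-way analysis of variance and the Cochran–Mantel–Haenszel test appear there only for secondary analyses.
- *Methods for additional analyses {20b}*: tests are chosen by type of variable, but this is said of secondary endpoints. It could not separate a t-test from a Mann–Whitney test anyway, since both apply to a continuous variable.
- *Sequence generation {16a}*: patients are assigned "using site-specific stratified block randomization with a 1:1:1 ratio".
- *Outcomes {12}*: day-1 NSE is measured and enters a secondary endpoint, the "difference in blood NSE on the 1st and 3rd day".
- *Sample size {14}*: the control group is planned at "a mean of 90 μg/L and a standard deviation of 80 μg/L", and it is assumed that any dose group "can lower the NSE level on the 3rd day to 40 μg/L or less". The design is stated with "power of 84%, one-sided alpha of 0.05, and dropout rates of 28"%.
- *Abstract, Methods*: different means, but an SD of 80 for both treated and control arms: "Assuming NSE of 42 ± 80 and 80 ± 80 μg/L in the treatment" arm and the control arm respectively.

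**The concern.** The two named tests answer different questions. The t-test compares means in μg/L; the Mann–Whitney test compares rank order. On skewed data they can disagree about significance, so the protocol does not settle what the primary result will be.

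The plan's own figures point to skew. NSE is a concentration and cannot be negative, yet the planned SD is up to twice the planned mean. On such data a raw-scale t-test is usually the less powerful of the two tests.

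The primary analysis also leaves information unused. Site is a stratification factor and is known for every patient. Day-1 NSE is already being collected. With 36 evaluable patients per arm, a few points of power matter if the true effect is smaller than planned.

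**Working it through.** **1. The plan's own figure.** Inputs from *Sample size {14}*: difference 90 − 40 = 50, SD 80, one-sided alpha 0.05, 50 per arm, 28% dropout.

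- Evaluable per arm: 50 × (1 − 0.28) = 36.
- z = 50 / (80 × √(2/36)) = 2.652.
- Power = Φ(2.652 − 1.645) = 84.3% (83.7% with the noncentral t).

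The stated 84% and 150 patients reproduce, for an unadjusted raw-scale comparison of one dose with placebo.

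**2. Skew implied by the inputs.**

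- SD/mean in control: 80/90 = 0.89.
- SD/mean in treated: 80/40 = 2.0, if the same SD applies. The abstract's values give 80/42 = 1.90 and 80/80 = 1.00.
- A normal variable with mean 40 and SD 80 is below zero with probability Φ(−40/80) = 31%.

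**3. Power of the candidate tests.** The log-normal shape is my assumption. The parameters are matched to the stated control mean and SD, and the treated arm has the same SD/mean ratio. There are 36 per arm, at one-sided 5%, with 60,000 simulated trials per scenario.

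| Control vs treated mean (μg/L) | Raw t | Mann–Whitney | t on log NSE |
|---|---|---|---|
| 90 vs 40 | 98.6% | 99.6% | 99.8% |
| 90 vs 55 | 77.4% | 83.8% | 85.5% |
| 90 vs 60 | 63.2% | 70.3% | 72.2% |

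The log column can be checked by hand. The log-scale SD is √ln(1 + 0.889²) = 0.763, with standard error 0.763 × √(2/36) = 0.180. At 90 vs 55, ln(90/55) = 0.492, z = 2.74 and power is Φ(2.74 − 1.645) = 86%. At 90 vs 60, ln(90/60) = 0.405, z = 2.25 and power is 73%. Using the t distribution in place of the normal gives 85.7% and 72.2%.

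The raw t-test therefore gives up about 6 to 9 points at the moderate effects and about 1 point at the planned one.

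**4. Error rate if the test is chosen on its result.** Under no effect, with log-normal data (mean 90, SD 80), the raw t-test rejects in about 5% of trials and so does Mann–Whitney. The smaller of the two p-values is below 0.05 in 7.0%. The figure is 7.3% for mean 40, SD 80, and 5.8% if NSE were normal. These are per dose comparison.

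**5. Adjusting for day-1 NSE.** A covariate with correlation ρ to the outcome multiplies the residual variance by 1 − ρ². The documents give no ρ. For an assumed range of 0.3 to 0.6 the variance falls by 9% to 36%, as if 36 evaluable patients were 36/0.91 = 40 to 36/0.64 = 56.

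**6. Adjusting for site.** The documents give no between-site variation in NSE, so the gain cannot be sized.

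**The case against.** The best defence is that naming the two tests together is common shorthand for a t-test if the data look normal and Mann–Whitney otherwise, and that the rule may stand in the SAP, which is not shown. This carries weight. With log-normal data at mean 90 and SD 80, a Shapiro–Wilk check in either arm rejects normality in 99.97% of simulated trials. A rule of Mann–Whitney after rejection, otherwise t, keeps the one-sided error at 4.9% and has Mann–Whitney's power (83% at 90 vs 55, 71% at 90 vs 60). The log-scale test is then only 1 to 2 points better than a test the plan already lists. What remains is that the protocol as written permits the raw t-test and states no rule.

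Several stronger readings are tempting but not supported.

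- **That the test will be picked by its p-value.** Nothing in the document says so. The 7% is conditional on it.
- **That the error is about 12% over two doses.** Two unadjusted dose comparisons with one fixed test already give about 8.6%. That is dose multiplicity, a separate matter, and should not be counted here.
- **That power falls from over 99% to 86% at 90 vs 40.** This arises only if SD 80 is kept at mean 40. The log-scale SDs are then 0.76 and 1.27, and the geometric means are 90/√1.79 = 67 and 40/√5 = 18, a far larger relative effect than 40/90. *Sample size {14}* states SD 80 for control only; the abstract does give it for both arms, but as a planning input.
- **That ignoring day-1 NSE is a proven loss.** The article does not say whether that sample precedes the first infusion. A post-dose value could carry part of the treatment effect and would be a poor covariate.
- **That omitting site invalidates the test.** Leaving out a stratification factor generally makes a test conservative. It does not inflate the error.
- **That the 84% is miscalculated.** It reproduces.

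**Conclusion.** The concern holds as a recommended improvement to the primary analysis. It does not show that the test is invalid or the sample size wrong. The protocol leaves two unadjusted tests open for its primary endpoint, with planning values that imply strong right skew, and makes no use of the stratification factor.

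If the raw t-test were the one used, the avoidable loss is about 6 to 9 points of power at 90 vs 55 and 90 vs 60, and about 1 point at 90 vs 40. These figures rest on a log-normal shape, an equal SD/mean ratio in both arms and 36 evaluable patients per arm. If Mann–Whitney were used, most of that loss disappears. If the choice were made on the results, the one-sided error would be about 7% per dose comparison.

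The skew argument and the open choice stand on the text alone. The gain from day-1 NSE is conditional on sample timing and on an undocumented correlation. The gain from site is real in principle but cannot be sized from the document.

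**What to change.** In *Statistical methods for primary and secondary outcomes {20a}*, replace the pair of tests with one primary analysis: a linear model on log day-3 NSE with treatment and site, reported as a ratio of geometric means with its confidence interval.

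Add log day-1 NSE as a covariate only if that sample is drawn before the first infusion, and state the timing. Otherwise adjust for site alone.

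Name a site-stratified Wilcoxon (van Elteren) test as the sensitivity analysis, so that the rank-based result is reported whatever the primary shows.

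The cost is wording. *Trial status* reports 89 of the planned 150 patients recruited as of May 15, 2022, and *Concealment mechanism {16b}* keeps assignment concealed until database lock, so on the document's account the change can be made before unblinding. The downside is that the result is read as a ratio and not as a difference in μg/L. If the SAP already fixes the test, the protocol wording should be brought into line with it.
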